## Abstract

**Background:**

Protracted amphetamine abstinence syndrome is one of the primary causes of relapse for amphetamine-type drug abusers during withdrawal. However, the importance of the management of protracted amphetamine abstinence syndrome is underestimated. Electro-acupuncture may be a safe and effective alternative therapy for protracted amphetamine abstinence syndrome, but the evidence is limited.

**Methods:**

The study is a prospective, two-center, randomized, waitlist controlled, open-label pragmatic trial. A total of 300 patients with protracted amphetamine abstinence syndrome will be recruited. All participants will be randomly assigned to an electro-acupuncture group or a waitlist group in a 1:1 ratio. Participants in the electro-acupuncture group will receive the electrical-acupuncture treatment. Waitlist group participants will not receive electro-acupuncture treatment but will be assessed at each visit. Treatments will be administered twice a week for a total of 4 consecutive weeks. The primary outcome in this study is the change in the ACSA between baseline (week 0) and the completion of treatment (week 4), and the secondary outcomes are changes in the Hamilton Depression Scale (HAMD), the visual analog scale (VAS), the Hamilton Anxiety Scale (HAMA), the Pittsburgh Sleep Quality Index (PSQI), the Montreal Cognitive Assessment (MoCA), and the Medical Outcomes Study 36-item Short-Form Health Survey (SF-36).

**Discussion:**

This study will assess the effectiveness of acupuncture in PAAS in real-world settings to provide support for clinical decisions and a basis for subsequent trials comparing acupuncture with other positive regimens.

**Trial registration:**

ClinicalTrials.gov ChiCTR2000040619. Registered on 3 December 2020

## Background

Amphetamine-type stimulants (ATS) are one of the most widely abused psychostimulative substances and are of highly addictive potential. Over the past few years, the increasing trend in ATS abuse has become a major public health problem around the globe. In 2019, around 27 million people worldwide, accounting for 0.5% of the global adult population, have used ATS [1], and more than one-third of these 27 million users was in East and South-East Asia [2]. The acute effects of ATS administration mainly include hallucination, sexual disinhibition, and irritation [3, 4], while chronic administration could cause cognitive impairments, social dysfunction, and multiple neuropsychiatric complications [5, 6]. There are also reports of severe consequences by overdose (e.g., hyperthermia, myocardial infarction, insomnia, and renal failure) [7]. Some ATS abusers will have to suffer long-lasting physical and mental symptoms such as body discomfort, depression, anxiety, and increasing drug craving even after a long time of withdrawal, which is defined as the “Protracted amphetamine abstinence syndrome (PAAS)” [8, 9]. The persistence of PAAS exerts an adverse impact on patients after ATS withdrawal, hinders them from backing to normal life, and probably accounts for relapse, which makes the clinical management of PAAS quite crucial.

However, there are still no medications available for the treatment with ATS use disorder, not to mention the PAAS [10], and cognitive behavioral therapy (CBT) and symptomatic treatment are the main approaches [11, 12]. However, CBT requires a great deal of infrastructure support for treatment providers, and transportation to the treatment site may also be difficult for some patients. Using therapists trained in CBT may be difficult for many programs [13]. Clinically, antipsychotics are commonly used in the treatment of ATS addicts, while typical antipsychotics have many adverse reactions, such as extrapyramidal symptoms and sedation [14].

Acupuncture is an important component of traditional Chinese medicine (TCM); currently, increasing studies showed that acupuncture could alleviate symptoms related to substance use disorders [15, 16], suggesting that it may offer a promising non-pharmacological approach for protracted abstinence symptoms, especially electro-acupuncture (EA). A comparative study showed that electro-acupuncture could alleviate withdrawal syndrome, anxiety, and depression in patients with methamphetamine addiction, with no side effects, no dependence, and no drug interaction [17]. A randomized controlled trial (RCT) published recently reported that compared with sham acupuncture, EA could effectively attenuate the symptoms of psychosis, anxiety, and depression during abstinence in methamphetamine addicts [18]. Though these studies yielded robust evidence of the efficacy of EA treatment for ATS addiction, especially for the protracted withdrawal syndromes, the RCT design with small sample size and strict inclusion criteria might limit the generalizability of the evidence.

Pragmatic randomized controlled trials (pRCTs) are randomized controlled design for comparing the results of different interventions in clinical practice in real or near-real medical environments [19]. pRCTs emphasize practical applicability and generalizability in real-world settings (external validity) and usually focus on the overall effectiveness rather than on the efficacy of the intervention [20]. Moreover, it allows complex intervention and takes into account the treatment will of patients, which makes it more feasible and suitable using the pRCT design to evaluate the clinical effects of acupuncture therapy [21]. Therefore, we propose a two-center, randomized, waitlist-controlled pragmatic trial to critically investigate the effectiveness of acupuncture in the treatment of patients with PAAS to provide a new direction for clinical management of ATS use disorder.

## Materials and design

### Objectives

The aim of this study is to assess the effectiveness of electro-acupuncture for patients with PAAS in clinical practice.

### Hypothesis

We hypothesize that eight sessions of EA treatment over 4 weeks will result in alleviation of protracted abstinence symptoms in patients with PAAS.

### Study design

This protocol also follows the updated CONSORT Statement (www.consort-statement.org), the Standard Protocol Items: Recommendations for Interventional Trials (SPIRIT) Checklist, and the standards for reporting interventions in clinical trials of acupuncture (STRICTA) guidelines [22–24].

A two-center, randomized, waitlist controlled, open-label pragmatic trial will be conducted, and a total of 300 patients are expected to be recruited from the Coercive Rehabilitation Center for Addicts Affiliated to the Public Security Bureau of Deyang City (Deyang 618000, P.R. China) and the Coercive Rehabilitation Center for Addicts Affiliated to the Public Security Bureau of Neijiang City (Neijiang 641000, P.R. China). Before the trial, all researchers will be given unified training. Placebo, sham acupuncture, and other placebo measures are generally not used as controls in pRCTs. A blank group can be adopted as a control if allowed by ethical principles, but the trial has to be conducted in a real-world setting [25]. The estimated duration of the main study phase is planned to last approximately 1 year. The flowchart of this study is shown in Fig. 1.

**Fig. 1 Fig1:**
[figure not shown]
Trial procedure flow chart

### Ethical approval

This study has been registered in the Chinese Clinical Trial Registry (identifier: ChiCTR2000040619, December 03, 2020.). The study protocol and informed consent (version no. 20210331, V3.0) have been systematically reviewed and approved by the Medical Ethics Committee of the Affiliated Hospital of the Chengdu University of Traditional Chinese Medicine (Approval No. 2019KL-067, September 21, 2020). All participants will voluntarily sign the informed consent form that has been approved by the ethics committee. Any important protocol modifications will be sent to the relevant parties through email.

### Participant recruitment and informed consent processes

The administrative staff of the Coercive Rehabilitation Center will be involved in the organization and supervision during the whole study process. Patients will be identified by a numerical code and no personal information will be included in the case report form (CRF) and the database or will be included in the publication. A detailed explanation of the study process will be provided by a trained researcher to the participants in a private room, which mainly includes the objective, methods, privacy security, possible risks, and participant rights. All participants will be informed that they can withdraw from the study at any time with the quit reasons recorded. All participants will be obtained their written informed consent prior to enrollment and kept one of the copies.

### Inclusion criteria

This study is designed as a pRCT based on a real-world setting. Broad inclusion and exclusion criteria are prearranged [25].
Patients aged from 18 to 60 who meet the diagnostic criteria in the Diagnostic and Statistical Manual of Mental Disorders, Fifth Edition (DSM-5) [26]Negative in a urine test for ATSWithout mental disorders or any other severe organic diseasesUninvolved in other clinical trials within 3 monthsSigned the informed consent form

### Exclusion criteria

Patients with any of the following conditions will not be included in this study:
Local trauma or infection around the acupointsIntolerance with EA and EA treatment or have a needle phobiaPregnant or breastfeeding women

### Stopping and withdrawal criteria

If the physician and the principal investigator assert that there are risks of serious adverse events during the study, it will be stopped. During the research, participation is completely voluntary, and participants have the right to withdraw from the trial for any reason at any time.

### Randomization

All participants will be assigned, in a 1:1 ratio, to the EA treatment group and waitlist group using stratified block randomization. The randomization sequence will be generated using a computer-based random-digit generator before the recruitment and will be blinded to investigators. Randomization information will be sealed in an envelope and will be unsealed by the corresponding participant after recruitment. The randomization sequence and envelopes will be stored by an associated team that will not be involved in other parts of this study.

### Blinding

Given that this study is a waitlist-controlled design, both the participants and acupuncturists cannot be blinded. All outcome measures will be conducted by a third party who does not participate in the trial. Statistical analysis will be performed by a statistical expert uninvolved in research and evaluation.

### Interventions

#### EA treatment group

Acupuncture will be performed by licensed acupuncturists who have more than 3 years of acupuncture clinical experience. The acupuncturists will be trained on the use of the semi-standardized protocol, reporting adverse events (AEs), and other experimental procedures and will only be involved in the acupuncture treatment.

The acupoint selection regimen was developed based on traditional acupuncture theories and our previous data mining for relevant articles [27]. The standardized section is composed of bilateral acupoint stimulation to Shenmen (HT7), Neiguan (PC6), Zusanli (ST36), and Sanyinjiao (SP6). Furthermore, the acupuncturist will be allowed to treat no more than three additional acupuncture points according to the individual conditions. The locations of the acupoints conform to the standard defined by the World Health Organization [28].

Disposable sterilized needles made of stainless steel (0.25 × 40 mm and 0.25 × 13 mm purchased from Huatuo, Suzhou Medical Supplies Factory Co. Ltd, Suzhou, China) will be applied in this trial. Acupuncture needles will be inserted to a certain depth to achieve the De Qi sensation. De Qi is indicative of effectiveness during acupuncture treatment and is characterized by dull pain, heaviness, aching, tingling, and numbness. After the achievement of De Qi, the SDZ-III EA apparatus (Huatuo; Suzhou, China) will be used for bilateral electrical stimulation at SP6 and ST36. The EA apparatus will be set to generate sparse and dense waves with frequencies of 2 Hz and 100 Hz, respectively, and a current of about 10–15 mA.

The treatment for the EA group will consist of 8 sessions of EA treatment with a duration of 30 min per session administered over a period of 4 weeks (2 sessions per week). Follow-up will last for 48 weeks after the treatment period with 4 visits to collect adequate relief data.

#### Waitlist group

The waitlist group patients will receive no treatments during the trial period. After 48 weeks of follow-up, they then will receive EA treatment the same as the EA group.

### Concomitant treatments

All participants could receive any other treatment during the trial. All treatments will be recorded on the CRF.

### Outcome measures

#### Primary outcome measures

Amphetamine Cessation Symptom Assessment (ACSA) is a clinician-based scale to assess withdrawal symptoms of patients with ATS addiction, which includes three subscales of “anxiety and mood,” “fatigue,” and “craving.” Items are scored on a 5-point scale ranging from 0 to 4 with higher scores representing more severe PAAS. The ACSA has been validated to be of high sensitivity, reliability, and specificity [29].

The change in ACSA scores will be measured at baseline, after the completion of treatment (week 4), and at the follow-up period (week 12, week 24, week 36, and week 48). The primary outcome in this study is the change in the ACSA between baseline (week 0) and the completion of treatment (week 4).

#### Secondary outcome measures

All the secondary outcomes will be measured at baseline, after the completion of treatment (week 4), and at the follow-up period (week 12, week 24, week 36, and week 48).

A visual analog scale (VAS) will be used to evaluate the craving for ATS [30]. Higher scores reflect a more severe craving for amphetamine.

Hamilton Depression Scale (HAMD-17) and Hamilton Anxiety Scale (HAMA-14) scores [31, 32] will be used to evaluate the severity of depression and anxiety, with higher scores indicating more severe symptoms of depression or anxiety.

Pittsburgh Sleep Quality Index (PSQI) was introduced in 1989 and is a valuable tool for assessing sleep-related problems, which contains 19 items with higher global scores reflecting worse sleep quality [33]. PSQI score will be applied in this study to assess the severity of insomnia.

Montreal Cognitive Assessment (MoCA) Beijing version will be applied to assess the cognitive performance. It contains 30 items, including 5 dimensions (executive function, language, orientation, memory, and abstraction) which is scored ranging from 0 to 30 with a higher score indicating better cognitive performance [34].

Medical Outcomes Study 36-item Short-Form Health Survey (SF-36) is a commonly used instrument for assessing the quality of life [35], which includes the following 8 dimensions: physical functioning, physical role functioning, social role functioning, bodily pain, mental health, emotional role functioning, vitality, and general health perception. SF-36 will be used in this study to assess the overall quality of life of PAAS patients.

### Safety assessment

The occurrence rate of adverse events (AEs), which include broken needles, unbearable needle tingling, local hematoma, infections, and any other discomfort or accidents, will be calculated as (number of cases with AEs/total number of cases)×100%.

The process of intervention will be monitored by a special squad. Participants who develop any adverse events will be managed by licensed clinicians, and all AEs will be collected, recorded, and reported.

### Adherence assessment

The sessions of treatments will be recorded in the CRF to assess the adherence of patients.

### Participant timeline

The participant timeline is described in Table 1.

**Table 1 Tab1:** Participant timeline

Study period	Baseline		Treatment				Follow-up			
Timepoint (week)	−1	0	1	2	3	4	12	24	36	48
**Participants**										
Screening	√									
Demography	√									
Informed consent	√									
Randomization		√								
Combined medication record	√	√	√	√	√	√				
**Interventions**										
EA group			√	√	√	√				
Waitlist group										
**Outcomes**										
ACSA	√					√	√	√	√	√
VAS	√					√	√	√	√	√
HAMD	√					√	√	√	√	√
HAMA	√					√	√	√	√	√
MoCA	√					√	√	√	√	√
PSQI	√					√	√	√	√	√
SF-36	√					√	√	√	√	√
**Trial safety evaluation**										
Adverse events			√	√	√	√				

*EA group*, electro-acupuncture group; *ACSA*, Amphetamine Cessation Symptom Assessment; *VAS*, visual analog scale; *HAMD*, Hamilton Depression Scale; *HAMA*, Hamilton Anxiety Scale; *MoCA*, Montreal Cognitive Assessment; *PSQI*, Pittsburgh Sleep Quality Index; *SF-36*, Medical Outcomes Study 36-item Short-Form Health Survey

### Quality control and trial monitoring

Regular monitoring will be performed by the trial team according to Good Clinical Practice (GCP) and Clinical Trial Unit standard operating procedures. Following written standard operating procedures, the monitors will verify that the clinical trial is conducted and data are generated, documented, and reported in compliance with the protocol, GCP, and the applicable regulatory requirements.

A trial steering committee (TSC) and data monitoring committee (DMC) will be convened and review trial progress every 6 months. The TSC will provide overall supervision of the trial and ensure its conduct is in accordance with the principles of GCP and the relevant regulations. The TSC will agree with the trial protocol and provide advice to the investigators on all aspects of the trial. The TSC will include members who are independent of the investigators, in particular an independent chairperson. The independent DMC will inform the TSC regarding the accruing trial and safety data, to ensure trial site staff and participants are aware of any relevant safety information and to advise the TSC regarding the appropriateness of continuation of the trial.

### Sample size

A total of 300 participants are expected to be recruited in this study (150 allocated to receive the EA group, 150 to the waitlist group), allowing for 20% loss to follow-up. Though a sample size of 300 participants is believed to ensure internal validity, a pilot study will be performed if the condition permits, given that there are currently no literatures that reported a change of ACSA scores in PAAS patients receiving acupuncture therapy to support the calculation of sample size.

### Data collection and management

The CRF will be documented by the doctors participating in the study, and in each selected case, it must be completed. After the completed CRF is reviewed by the clinical supervisor, the original form will be handed over to the data manager for data entry and management. The trial will set up a database using EpiData2.1 to manage the study data. All electronic data will be secured on a password-protected laptop. The trial statisticians will have access to the data set for the final analysis of trial outcomes. The CRF will be stored in the Acupuncture & Moxibustion Laboratory at Chengdu University of Traditional Chinese Medicine (Chengdu, China). The clinical trial data will be kept for at least 5 years after which it will be destroyed and deleted.

### Measures to improve compliance

Establishing a good relationship between doctors and patients, and providing participants with subsidies for costs.

### Statistical analysis

The statistical analysis will be conducted by independent third-party professional statisticians and will be performed using SAS (Ver9.4). All statistical analyses will follow the principle of intention-to-treat (ITT). All patients who underwent randomization will be included in the final analysis. A two-sided test at a significance level of 95% is deemed as statistically significant.

For the description of baseline features, the mean with the standard deviation or range with the minimum and maximum will be used for continuous data. For homogeneity tests of baseline characteristics between the two groups, a two-sample *t*-test will be used for continuous data. If there are baseline characteristics that exhibit statistically significant differences between the groups, analysis of covariance or logistic regression will be used for analysis and adjustment of the baseline characteristics.

A generalized linear mixed-effects model will be employed to analyze the primary outcome and other repeatedly measured outcomes. Randomization, baseline assessments, stratification factors, assessment times, and time-intervention interaction will be included in the regression models as covariates. It could be used to assess within-participant correlations due to repeated measurements, as well as between-group variations. A *p*-value of less than 0.05 will be considered to indicate statistical significance.

Compliance will be represented primarily by the number of treatment sessions attended. Participants had good compliance, with treatment of more than 80%.

For the comparison of AEs and combined use of drugs between groups, a *χ*^2^ test or Fisher’s exact test will be performed. The data for AEs will be collected from symptoms reported by the patients, and observations by a researcher.

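### Intention-to-treat is applied to every analysis, so EA-allocated participants who are never needled would enter the adverse event denominator (minor)

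*Protocol article*

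**What the plan says.** The Statistical analysis section sets one rule for everything: "All statistical analyses will follow the principle of intention-to-treat (ITT"). It adds: "All patients who underwent randomization will be included in the final analysis". Later in the same section comes the safety test, introduced by "For the comparison of AEs and combined use of drugs between groups", with a chi-square or Fisher's exact test. Nothing there exempts AEs from the general rule.

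The Safety assessment section defines the AE rate, which "will be calculated as (number of cases with AEs/total number of cases"), expressed as a percentage. It does not say what a case is, which arm is meant, or whether a case must have received treatment. The events counted are "broken needles, unbearable needle tingling, local hematoma, infections, and any other discomfort or accidents".

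The planned arms are given as "150 allocated to receive the EA group, 150 to the waitlist group". The Adherence assessment section says that treatment sessions are recorded on the case report form (CRF), so exposure will be known for each participant.

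**The concern.** Intention-to-treat protects an effectiveness comparison from selective exclusion after randomisation. A harm rate usually answers a different question: how often does a person who receives the treatment have an event? A broken needle or unbearable needle tingling cannot happen to someone who was never needled, and the haematomas and infections are listed in the same context. Under the stated rule, an EA-allocated participant who never starts is counted as if exposed and is certain to be free of needling events. Any such participant lowers the reported needling rate.

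The Abstract presents EA as possibly safe as well as effective, so readers will probably take the AE rate as the risk of having EA. As written, it is the risk of being allocated to EA. The two are equal only if everyone starts.

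**Working it through.** **No stated figure to reproduce.** The protocol gives no expected AE rate, no safety denominator and no non-start rate. The calculation shows what the rule does under assumed values.

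**Inputs**
- EA arm: 150 randomised (Sample size section).
- Rule: all analyses by intention-to-treat, everyone randomised included (Statistical analysis section).
- u, the share of the EA arm never needled: not given; assumed 0%, 2%, 5% and 10%.
- r, the needling-related AE rate among those treated: not given; assumed 5%, 10% and 20%.

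**Formula.** Participants treated = 150 × (1 − u). Expected number with a needling event = r × 150 × (1 − u). Over all randomised, the rate is r × 150 × (1 − u) / 150 = (1 − u) × r. The relative understatement equals u.

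**Numbers for r = 20%**
- u = 0%: 150 treated, 30 expected, 30/150 = 20.0%.
- u = 2%: 147 treated, 29.4 expected, 29.4/150 = 19.6%.
- u = 5%: 142.5 treated, 28.5 expected, 28.5/150 = 19.0%.
- u = 10%: 135 treated, 27 expected, 27/150 = 18.0%.

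On the treated denominator the rate is 20% in every row.

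**Other assumed rates, for u = 2%, 5% and 10%**
- r = 10%: 9.8%, 9.5% and 9.0%.
- r = 5%: 4.9%, 4.75% and 4.5%.

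**An event never observed.** The exact one-sided 95% upper limit is 1 − 0.05^(1/n). It is 1.98% for n = 150 and 2.19% for n = 135 (u = 10%).

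**Effect on the between-group test.** Assume a true EA rate of 10% and a waitlist rate of 1%. For u = 5%, power is 0.914 over all randomised and 0.926 with the treated denominator. For u = 10%, it is 0.893 and 0.920.

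**Limit of the formula.** It holds for events that need a needle. If un-needled EA participants have other events at rate s, the all-randomised rate is (1 − u) × r + u × s. This is below r only when s is below r, so the general discomfort category is diluted less, or not at all.

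**The undefined denominator.** If the case total in the Safety assessment section meant all 300 participants, an EA rate of 10% would appear as 15/300 = 5%, even with no non-starters. The between-group comparison in the Statistical analysis section points to a per-arm denominator, so this reading is less likely, but the wording does not exclude it.

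**The case against.** The best argument on the other side is that safety sets are normally defined in a statistical analysis plan, which is not shown, and that a journal article condenses. The absence of a safety set is indeed no fault. What remains is a positive statement that covers all analyses: a later plan using a treated-only set for AEs would contradict it.

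Second, the case total is undefined and could mean treated participants. That is so. The all-randomised reading comes from taking the two sections together.

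Third, the design gives reasons to expect few non-starters. Both sites are rehabilitation centres whose staff organise and supervise the study, people with needle phobia or EA intolerance are excluded, and sessions begin the week after randomisation. This stands as a limit on size. Non-start is still possible, because allocation is open-label and participants may leave at any time.

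Fourth, comparing AEs by allocated group preserves randomisation and suits a pragmatic trial. This is a good reason to keep that comparison, but not to have it as the only one.

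A reader might infer three stronger points that the document does not support:
- **The 20% in the Sample size section as an upper bound for non-starters.** It is an allowance for loss to follow-up, in a trial with visits to week 48, while Table 1 schedules AE recording only in weeks 1 to 4. A participant lost at a late visit has already been needled and observed, and belongs in either denominator. The same holds for anyone who leaves after a first session.
- **Waitlist participants being needled, so that their events count against the waitlist arm.** The Concomitant treatments section does say "All participants could receive any other treatment during the trial", but the Waitlist group section withholds EA until follow-up is over, and nothing indicates that needling would be available elsewhere.
- **The rule making EA look safer in every case.** It has no effect if all EA participants start, and little or none on events that do not depend on needling.

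**Conclusion.** The point holds as a minor one. The protocol states a rule, rather than merely leaving a gap, that puts the AE comparison under intention-to-treat, and it pairs that rule with an undefined denominator. Read together, they understate the needling-related AE rate in the EA arm by the share never needled.

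That share is not in the document. Over an assumed range of 0% to 10%, a true rate of 20% is reported as 20% down to 18%, and the actual effect is probably near the small end. It would be unlikely to change a conclusion about safety. The result rests on reading the case total as everyone randomised to the arm, and on counting events that require needling.

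**What to change.** Make two wording changes and add one table.

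1. In the Statistical analysis section, limit the intention-to-treat sentence to the effectiveness outcomes.
2. In the Safety assessment section, replace the undefined case total with a rate stated per arm. For EA, the denominator is participants who received at least one session; the comparator is the waitlist participants.
3. Show the comparison of all randomised participants, by allocated arm, alongside. Report the number of EA participants who had no session, so that readers can see how far the two rates can differ.

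No new data are needed, since sessions are already on the CRF. The cost is that the treated-only comparison is not strictly randomised, which is why the all-randomised one should stay beside it, and that the headline AE rate may be slightly less favourable.

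### Baseline significance tests trigger a further adjusted analysis, selected by chance imbalance, and its relation to the fixed mixed model is not stated

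*Protocol article*

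**What the plan says.** Three rules stand one after another in the protocol article, Statistical analysis.

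1. Baseline comparison: "For homogeneity tests of baseline characteristics between the two groups, a two-sample *t*-test will be used for continuous data".
2. Trigger: "If there are baseline characteristics that exhibit statistically significant differences between the groups, analysis of covariance or logistic regression will be used". The sentence goes on to say that this serves both analysis and adjustment of the baseline characteristics.
3. Outcome model: "A generalized linear mixed-effects model will be employed to analyze the primary outcome and other repeatedly measured outcomes". Its terms are fixed: "Randomization, baseline assessments, stratification factors, assessment times, and time-intervention interaction will be included in the regression models as covariates".

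The Randomization section gives the allocation method: "All participants will be assigned, in a 1:1 ratio, to the EA treatment group and waitlist group using stratified block randomization". The threshold is given as "A *p*-value of less than 0.05 will be considered to indicate statistical significance". No separate threshold is given for the baseline tests, so 0.05 is taken to apply to them too.

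**The concern.** With sound random allocation, any baseline difference between arms arises by chance. The baseline t-tests therefore test a null hypothesis that is true by design, and their result says nothing about whether a variable needs adjustment. A variable unrelated to the outcome is brought in if its p-value happens to fall below 0.05. A strongly prognostic one is left out if its p-value is just above.

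The second difficulty is overlap. The triggered analysis and the mixed model both apply to the efficacy outcomes, and the article does not rank them. If the trigger fires, a statistician following the text cannot tell whether to report the mixed model as specified, the mixed model with added covariates, or a separate ANCOVA. At stake is which number is the primary estimate of the electro-acupuncture effect, and whether that was settled before the data were seen.

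**Working it through.** **Is any outcome left for the triggered analysis?** The outcome sections list ACSA, VAS, HAMD, HAMA, PSQI, MoCA and SF-36. All are scale scores measured at baseline and at weeks 4, 12, 24, 36 and 48, so rule 3 covers all of them. Adverse events and concomitant drug use have their own chi-square or Fisher test. Every outcome thus has a method without rule 2, and no binary efficacy outcome is defined for the logistic regression.

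**How often would the trigger fire by chance?** The article attaches no figure to this rule, so there is none to reproduce. It also does not list the variables to be tested; the counts below are assumptions drawn from the outcome list:
- 7 scores: the seven instruments, one score each.
- 14 scores: six scales plus the eight SF-36 dimensions.

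For k independent tests at 0.05, P(at least one significant) = 1 − 0.95^k:
- k = 7: 1 − 0.95^7 = 0.302
- k = 14: 1 − 0.95^14 = 0.512

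Symptom scales are correlated, which lowers these figures. Simulation with equal correlation between scores (150 per arm, 4,000 runs) gave:

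| Scores tested | independent (formula) | correlation 0.3 | correlation 0.5 |
|---|---|---|---|
| 7 | 30% | 27% | 23% |
| 14 | 51% | 43% | 35% |

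The correlations are assumed. Testing demographic variables as well would raise the figures.

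**What happens to error rates?** The Sample size section gives 150 per arm and allows 20% loss: 150 × 0.80 = 120 per arm. It gives no effect size or SD, so the effects below are assumed.

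*Mixed model extended by the triggered covariates.* The outcome's own baseline is always in the model, and any of 14 further covariates (inter-correlation 0.4) is added if its t-test is significant:
- Type I error: 4.3-5.2% with the trigger, 4.4-5.2% without.
- Power at an assumed 0.364 SD: 90% and 98% with the trigger (correlation of own baseline with outcome 0.5 and 0.7), against 90% and 97-98% without.
- Always including one truly prognostic extra covariate (coefficient 0.2-0.3 SD) gains about 1-3 percentage points of power. That is the approximate cost of choosing covariates by imbalance.

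*No adjustment unless triggered.* This is not what the article's mixed model does, but it bounds the problem. Adjusting for a covariate only after a significant baseline test gave type I error of 3.9-4.9%, against 4.9-5.2% for always adjusting (8,000 runs). Even here the rule is conservative.

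**The case against.** The strongest defence is that the mixed model is named without condition for the primary outcome and always adjusts for baseline. Nothing says that the trigger removes it, so the natural reading is that the trigger adds something. If the baseline assessments in that model mean all the baseline scales, the trigger could add only variables outside them, such as demographics. This defence stands, and it rules out several stronger readings that a reader might infer.

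- *That chance imbalance chooses the primary analysis.* This is true only if the triggered ANCOVA replaces the mixed model or alters its covariates. The text leaves that open and does not say it.
- *That much power is lost.* With an assumed 0.3 SD effect, 120 per arm and baseline correlations of 0.3, 0.5 and 0.7, always adjusting gives about 68%, 76% and 90% power. Adjusting only when triggered gives about 64%, 65% and 66% if the default is an unadjusted follow-up score. That default is not in the plan, so the gap does not carry over.
- *That the 5% level fails.* Followed mechanically, it does not. It would be exceeded if someone could report the smaller of two p-values. One simulation under assumed prognostic strengths put that at 6.1-6.8%, and the excess shrinks when the added covariates are less prognostic. The article does not exclude such a choice, but it does not describe one either.
- *That an unblinded trial team would make the choice.* The Blinding and Statistical analysis sections give the analysis to statisticians outside the trial. They are not said to be blind to allocation, but they are not the treating team.
- *That logistic regression has no possible use.* Adverse events, drug use and the 80% compliance threshold are binary. An adjusted analysis of these is conceivable, though the article assigns none.

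It can also be said that a condensed article leaves precedence and covariate lists to the analysis plan. That would answer a complaint about silence. It does not answer this point, because the article states the significance-triggered rule outright.

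**Conclusion.** The point holds in a limited form. The article contains a rule that makes adjustment depend on significance tests of chance differences, next to an unconditional mixed model for the same outcomes, with no statement of how the two relate. Chance alone would fire the trigger in about 23-30% of repetitions with 7 baseline scores and 35-51% with 14. These ranges rest on assumed variable counts and on correlations from 0 to 0.5.

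The consequence is a covariate set that depends on the data and a primary estimate that is unclear whenever the trigger fires. Type I error is not inflated by following the rule. Where the mixed model stays in place, the power cost is small, about 1-3 points against naming a truly prognostic covariate in advance. This is a correction to the stated rule and does not put the trial's validity in doubt.

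**What to change.** In the Statistical analysis section:
- Delete the homogeneity tests and the sentence that triggers ANCOVA or logistic regression. Describe baseline by arm without p-values.
- State that the mixed model is the sole primary analysis. Name its covariates: the baseline value of the outcome analysed, the stratification factors, and any prognostic factors fixed before anyone sees data by arm.
- Label any further covariate adjustment as a sensitivity analysis.

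The cost is a few sentences of wording, with no change to recruitment, visits or data collection and slightly less analysis work. The change should be made before outcome data are seen by arm, because settling precedence afterwards would itself depend on the data.
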